**Methods:**

A parallel-group, block-randomized clinical trial will compare ePT and uPOD. Both groups will be seen initially by a podiatrist before allocation to a group that will receive physical therapy intervention consisting primarily of manual therapy, exercise, and modalities, or podiatric care consisting primarily of a stretching handout, medication, injections, and orthotics. Treatment in each group will be directed by practice guidelines and a procedural manual, yet the specific intervention for each participant will be selected by the treating provider. Between-group differences in the Foot and Ankle Ability Measure 6 months following the initial visit will be the primary outcome collected by an independent investigator. In addition, differences in the European Quality of Life – Five Dimensions, Numeric Pain Rating Scale, Global Rating of Change (GROC), health-related costs, and cost-effectiveness at 6 weeks, 6 months, and 1 year will be compared between groups. The association between successful outcomes based on GROC score and participant expectations of recovery generally, and specific to physical therapy and podiatry treatment, will also be analyzed.

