### Participants

Individuals presenting with a primary complaint of PHP to the Podiatry Department of the Des Moines University Clinic will be recruited for this study. Participants will be included if they have a primary clinical diagnosis of PHP determined by having tenderness to palpation of the plantar aspect of the heel and pain associated with first step after waking in the morning or with progression of weight-bearing during the day. Eligible participants will be between the ages of 18–60 and demonstrate a score of less than 74/84 on the FAAM activities of daily living (ADL) subscale to allow for improvement of at least the minimum clinically important difference [30]. Participants will be excluded if they had prior surgery of the foot, ankle, or lower leg; clinical signs of radiculopathy; contraindications to manual therapy interventions (i.e., tumor, fracture, rheumatic inflammatory disease [rheumatoid, reactive and psoriatic arthritis, inflammatory bowel disease, ankylosing spondylitis, and systemic lupus erythematosus], osteoporosis, prolonged history of steroid use, severe vascular disease, etc.); clinical indication of plantar fascia rupture; are unable to complete questionnaires; unable or unwilling to comply with treatment recommendations of either treatment group; or had prior treatment for PHP in the past 6 weeks. In addition, individuals who have a body mass index (BMI) greater than 30 kg/m^2^ or symptoms for longer than 1 year will be excluded due to the greater risk of chronic symptoms and poor response to conservative management [4,6,13,31].

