Participant expectations and preferences for ePT or uPOD will be categorized into three categories; matched, unmatched, and neutral. Participants will be labelled ‘matched’ if they are allocated to a group for which they have expressed a higher expectation of benefit. A higher expectation will be denoted by comparison of visual analog ratings between the groups (ePT and uPOD; Additional file 1). Unmatched participants will be those who are allocated to the treatment group for which they have a lower expectation of benefit. Neutral participants will be those who indicate the same level of expectation for both treatments. Similar categorizations will be made for participant preference based upon their response to the treatment preference question (Additional file 1). General expectations of improvement will be dichotomized into met or unmet based upon rankings at the 6-week, 6-month, and 1-year follow-up relative to baseline rankings. Participants that demonstrate 6-week, 6-month, and 1-year ranks equal to or higher than baseline will be considered to have met their global expectations of improvement. Participants that demonstrate rankings below baseline expectations will be considered to have unmet global expectations of improvement. A χ^2^ test of independence will be used to compare the proportions of individuals with matched/unmatched/neutral expectations or preferences to global expectations (met or unmet). In addition, differences in expectation and preference categories will be analyzed relative to treatment success using a χ^2^ test of independence. Treatment success will be determined by the GROC at each period with success defined as a GROC of +5, “a great deal better”, or greater.

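### The expectation and preference chi-square has no term for allocated arm, so a treatment effect can pass for, or hide, an effect of matching if opinion is lopsided and GROC success differs between arms

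*Protocol article*

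**What the plan says.** The second part of the Statistical analysis section of the protocol article defines the classification: "Participant expectations and preferences for ePT or uPOD will be categorized into three categories; matched, unmatched, and neutral". The rule is: "Participants will be labelled ‘matched’ if they are allocated to a group for which they have expressed a higher expectation of benefit". Unmatched participants are those allocated to the treatment they rated lower, and neutral participants rated both the same. Preference is classified in the same way from a separate question.

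The three-level variable is then tested twice with a chi-square test of independence:

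- against whether general expectations of improvement were met or unmet at follow-up;
- against treatment success ("differences in expectation and preference categories will be analyzed relative to treatment success using a" chi-square test), where "Treatment success will be determined by the GROC at each period with success defined as a GROC of +5" or greater.

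Neither test is described as done within arm or adjusted for arm. The only adjustment in the section is an analysis of covariance, used if participant characteristics differ between groups. It does not apply to these chi-square tests. The abstract announces the analysis among the study's results: "The association between successful outcomes based on GROC score and participant expectations of recovery generally", and also expectations specific to each of the two treatments.

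**The concern.** The label combines a baseline attitude with the randomised allocation. If most participants favour podiatry, most matched participants are in uPOD and most unmatched participants are in ePT. One table across both arms then compares, in part, uPOD with ePT. Any difference in GROC success between the treatments, which the trial itself examines, enters the result as though it came from expectation or preference.

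The error can go either way. A plain treatment effect could be published as evidence that expectation drives recovery, or a real benefit of matching could be cancelled. A lean in one direction is plausible, because the trial recruits "Individuals presenting with a primary complaint of PHP to the Podiatry Department" and everyone has a podiatry visit before enrolment. The same problem affects the met/unmet outcome, which also depends on the follow-up GROC.

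**Working it through.** **Inputs from the protocol.** There are two arms of 56. The plan's own figure reproduces: 9/14.5 = 0.62; the exact two-sided t-test at alpha 0.05 has 80.3% power with 42 per group and 79.3% with 41; 42 × 1.33 = 55.9, so 56. Allocation is taken as 1:1 because equal groups are planned. The protocol states no figure for the expectation analysis.

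**Assumed inputs.** The split of opinion and the success rates are not in the protocol, so a range is shown.

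**Formula.** Let p be the share of non-neutral participants favouring ePT, and s_E and s_U the success rates in ePT and uPOD. Under 1:1 allocation a proportion p of matched participants, and 1−p of unmatched participants, are in ePT. With no effect of matching:

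- matched success = p·s_E + (1−p)·s_U
- unmatched success = (1−p)·s_E + p·s_U
- gap = (2p−1)·(s_E − s_U)

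The gap is zero if p = 0.5 or if s_E = s_U.

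**Worked case.** Take 70% favouring podiatry, 20% physical therapy and 10% neutral, with success 60% ePT and 40% uPOD. Then p = 0.2/0.9 = 0.222. Matched success = (0.7×0.4 + 0.2×0.6)/0.9 = 44.4%. Unmatched success = (0.7×0.6 + 0.2×0.4)/0.9 = 55.6%. The gap is −11 points although matching does nothing.

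**False-positive rates.** These come from simulation with 56 per arm, no matching effect and a nominal 5% level. Splits are podiatry/physical therapy/neutral.

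| Split | Success ePT v uPOD | p | Spurious gap (points) | Chi-square across both arms |
|---|---|---|---|---|
| 45/45/10 | 60% v 40% | 0.50 | 0 | about 5% |
| 50/30/20 | 60% v 40% | 0.375 | −5 | 6–7% |
| 70/20/10 | 55% v 45% | 0.222 | −6 | 7–8% |
| 70/20/10 | 60% v 40% | 0.222 | −11 | 15–17% |
| 80/10/10 | 60% v 40% | 0.111 | −16 | about 27% |
| 80/10/10 | 70% v 40% | 0.111 | −23 | about 56% |

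A Cochran–Mantel–Haenszel test stratified by arm rejected in about 4–5% of trials in these settings. With equal success in both arms, the unstratified test also stayed near 5% whatever the split. With 42 per arm the inflation is somewhat smaller: about 12% for 70/20/10 at 60% v 40%.

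**Direction.** With 30% neutral and 70% v 40% success, p = 0.8 gives a gap of +18 points (28% rejection) and p = 0.2 gives −18 points (28%). The sign follows whichever arm is favoured.

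**Masking.** In the last row of the table, a true benefit of matching of 20 points would appear as 20 − 23.3 = −3.3 points.

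**The case against.** The strongest reply has four parts.

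1. **The confounding is conditional.** A reader might infer that matched status is confounded with treatment by construction. It is not. With an even split, randomisation makes the label independent of arm and the test holds its level. Bias needs both a lopsided split and a difference in GROC success. The label also follows the allocated group, so the confounding is with allocation and not with treatment received.

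2. **Every size is assumed.** The protocol does not say that participants lean towards podiatry. The Participants section excludes people unable or unwilling to follow either treatment, which may remove the strongest preferences. Mild settings give only 6–8%, and the 56% figure needs an extreme split and a 30-point difference together.

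3. **Pooling is inferred.** The text is silent on whether the table is formed overall or by arm.

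4. **The analysis is peripheral.** It belongs to none of the three specific aims, and the separate between-arm GROC comparison would alert readers to a treatment difference.

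All four limit the point, and none removes it. Neither condition can be ruled out in advance, so the test's validity depends on how opinion happens to fall. One table across both arms is the natural reading of a three-level variable that spans them. The protocol's caution that secondary analyses may be underpowered does not help, because this is bias and not low power.

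**Conclusion.** The point holds in conditional form. The stated test does not separate matching from allocated arm, and the distortion is (2p−1) times the arm difference in the outcome. Under the assumed values with 56 per arm, the false-positive rate runs from the nominal 5% (even split, or equal success) through 15–17% to about 56% at the extreme. None of these rates is a forecast, because the protocol supplies neither the split nor the success rates. A reader might go further and conclude that the analysis is bound to mislead, or that the trial's main result is compromised. The document supports neither: the primary FAAM analysis and the between-arm GROC comparison do not use this variable. The matter is minor to moderate and worth correcting because a better test is available from the same data.

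**What to change.** For both outcomes (GROC success and met/unmet expectations), and for expectation and preference separately, replace the chi-square test with a Cochran–Mantel–Haenszel test stratified by allocated arm. Logistic regression on arm and category, with their interaction examined, would serve equally. The interaction matters because a matching contrast that reverses between arms suggests that the direction of preference is itself prognostic. Show the matched/unmatched/neutral tables by arm and label the results exploratory.

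The cost is a change of wording. Allocation, baseline ratings, preference and GROC are already collected, and in the settings examined the stratified test kept its level when opinion was balanced as well as when it was not.

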### Economic evaluation

An economic evaluation will be conducted alongside this randomized clinical trial in accordance with established methods [58,59]. Costs and consequences of ePT and uPOD from the viewpoint of a healthcare payer and society will be estimated using billing records and a participant-reported questionnaire at all follow-up time points. Incremental cost effectiveness will be reported using quality-adjusted life-years derived from the EQ-5D™ and index scores from the United States [37]. A separate protocol paper will describe the methods of the economic evaluation in greater detail and in accordance with recommendations from publication guidelines for economic evaluations [60].

## Discussion

This paper describes the methods of a randomized clinical trial comparing ePT and uPOD for PHP. The proposed work builds on emerging evidence indicating the benefit of early physical therapy intervention [27-29], which has not been established in a population of individuals with PHP. In addition, previous investigations have analyzed the outcome associated with individual or 1–2 combined interventions for PHP. This is the first pragmatic study, as far as we are aware, that investigates the role and cost-effectiveness of impairment-based physical therapy intervention early in the multi-disciplinary management of PHP. The implications of this work address national concerns about rising healthcare costs in the American healthcare system, will help inform clinical guidelines, and benefit multiple healthcare providers involved in PHP management. This trial is registered at clinicaltrials.gov, identifier NCT01865734 to increase transparency of trial. The results of this investigation will be submitted for publication in peer-reviewed journals and presented at local and national meetings regardless of the outcome. The Orthopaedic Section, APTA, Inc. will be credited for monetary support provided for this work in all publications and presentations.

### Limitations

This study will be the first to compare uPOD and ePT and this investigation will be conducted at one location, the Des Moines University Clinic. As a result, the findings may have limited generalizability to other settings. In addition, treatments provided by both groups will be done at the discretion of the provider. There will be six Podiatrists and four Physical Therapists providing treatment, which may result in variation of treatment within each group. Efforts will be made to reduce variation by providing a guide based upon current best evidence for the physical therapy intervention (Tables 2 and 3), but the intent of this trial is to capture the value and differences of pragmatic clinical approaches used to manage PHP. This may result in difficulty describing specific details about treatment beyond reporting of Current Procedural Terminology codes used when treatment is billed, but general aspects of treatment will be described in as much detail as possible.

The inclusion and exclusion criteria used in this investigation will help to reduce the likelihood of confounding factors but will also limit the generalizability of results. The results of this investigation may not apply to individuals with a BMI greater than 30 kg/m^2^, PHP symptoms for longer than 1 year in duration, older than 60 years of age, or comorbid conditions that were excluded in this trial (e.g., osteoporosis, rheumatic inflammatory diseases, severe peripheral artery disease).

All participants in this study will be seen by a podiatrist first and therefore the results of this investigation will apply to clinical scenarios when an individual presents first to podiatry with PHP. Preliminary unpublished investigation at the Des Moines University Clinic indicates that a significant majority of patients present first to podiatry than to any other specialty for PHP, but no other investigations were found to describe the prevalence of patient presentation to the primary providers for PHP. Therefore, the design of this trial is based upon local patterns of patient entry to the healthcare system for PHP. The results of this investigation may be limited in clinical scenarios where the patient may present to another provider first or does not receive an evaluation and treatment from a podiatrist initially.

## Abbreviations

ACFAS: American College of Foot and Ankle Surgeons; ADL: Activities of daily living; APTA: American Physical Therapy Association; BMI: Body mass index; ePT: Early physical therapy; EQ-5D™: European quality of life-five dimensions; FAAM: Foot and ankle ability measure; IRB: Institutional Review Board; MCID: Minimum clinically important difference; NPRS: Numeric pain rating scale; PHP: Plantar heel pain; uPOD: Usual podiatric care.
